## 3. Methods

### 3.1. Study Design and Settings

A two-arm parallel-group cluster-randomized controlled trial (cRCT) will be conducted among hypertensive patients in Bangladesh and Pakistan. In the first stage, two districts in Bangladesh were chosen randomly: Rangpur district and Chuadanga district. In the second stage, from each district, one subdistrict was selected randomly: Pirganj and Alamdanga. Finally, 20 pharmacies were chosen from each subdistrict to reach our target sample. The overall flow of the study is shown in Figure 1. Randomization clusters are community pharmacies. Each country will follow a two-arm cRCT design. According to a 4.65% BP reduction with a standard deviation of 49.78 [27], the estimated sample size for Bangladesh is around 3600 at 80% power and 5% significance. Approximately 10% of participants will be selected based on a Bangladesh sample from Pakistan (360 hypertensive patients from four pharmacies). The average number of hypertensive patients per pharmacy is 90. Due to financial limitations and logistical challenges, it is necessary to choose 10% of the participants from Pakistan. This decision was primarily influenced by the availability of resources and the specific focus of our research project. These limitations included budget constraints that impacted the scope of the study and logistical challenges related to the larger geographic and infrastructural differences between the two countries. Conducting a full-scale study in Pakistan similar to Bangladesh is not feasible with the available resources. However, by including participants from Pakistan, we aim to enhance the diversity within our study population, despite some similarities in sociodemographic profiles and health behaviors between the two countries.

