### 3.6. Intervention

This project will consist of three phases: baseline survey with first-time intervention implementation; second intervention at 6 months; and third, endline survey at 12 months. The details of the intervention content are mentioned in Table 1. As part of the intervention within the randomized selected groups, the CP will conduct two 15–30 min sessions throughout the intervention period, once at the baseline or first visit (T0) and once at the sixth month (T1). Patients will attend the two sessions at the pharmacies where they collect their prescription medication. Face-to-face counseling sessions will be held about hypertension and its management, including lifestyle changes and drug compliance. Patients will be able to view the educational material in the pharmacy via a tablet since audio–visual presentations make learning easier. The detailed training material and handbook are presented as Supplemental Files S1 and S2. To maintain adherence to intervention, the intervention group will receive phone call intervention at 3 months and 6 months. The patient will be reminded every time about their subsequent visits via phone calls/short message services (SMS). Patients’ BP will be monitored routinely during each session, and information regarding medication and complications will also be obtained. This intervention will be low in cost, aligned with the current CP workflow, and will not require any significant changes in the existing system. Both interventions will be conducted by the same pharmacist to ensure consistency. Furthermore, CPs in the intervention group will receive a checklist of items and a counseling protocol to prepare them for what they need to do during patient visits. A pilot study was conducted in two pharmacies in Bangladesh before starting the study in order to optimize the intervention steps and materials. Nevertheless, there are no restrictions on how many times the patient may meet the pharmacists outside of these ‘core’ consultations. In this case, the patient will decide with the pharmacist according to needs, and it is suggested that this coincides with the monthly collection of prescriptions.

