### 3.8. Outcome Evaluation

The primary effectiveness of the outcome will be evaluated by changes in the SBP and DBP of the patients from baseline to final follow-up at 12 months post-intervention. The secondary outcome measures will include (1) BP controlled to target (SBP < 140 mmHg and DBP < 90 mmHg); (2) composite outcome of death (all-cause) or hospital admission due to CHD, heart failure, or stroke; (3) incremental cost per HRQoL gained from baseline to end of follow-up; (4) improvement in the knowledge of patients on healthy lifestyle; (5) change in dietary salt intake; (6) change in quality of life; (7) change in the prevalence of current smokers; and (8) the treatment adherence rate. Hypertensive patients with poor adherence to their treatment regimens experience uncontrolled blood pressure. Adherence to hypertension treatment is defined as following the treatment regimen agreed to with their physician. According to the previous literature [29,30,31], a reduction of 5 mmHg of SBP is considered clinically relevant as it has been found to be significantly associated with a risk reduction in CHD, stroke, and other serious cardiovascular events. Health service utilization parameters will include the number and reason for visits to physicians and hospital admission, and when further complicated, the death of the patient. The cost-effectiveness measures are incremental cost per mmHg BP reduction or cost per HRQoL gained from baseline to end of follow-up at 12 months. For determining dietary salt intake level, a 24 h urinary sodium measurement will be opted.

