### 3.13. Statistical Analysis

All outcomes will be analyzed using the intention-to-treat principle. Descriptive statistics will be used to present baseline characteristics and outcome variables. Percentages and frequencies will be used for categorical variables, and means and standard deviations will be used for continuous variables. Baseline characteristics between the two arms will be compared with chi-square or Fisher’s exact test, as appropriate. A multilevel mixed model will be used to compare the differential changes in each outcome across the time points (T1, T3, and T5) to measure the primary and secondary outcomes. We will analyze group changes (with individual pharmacies treated as a random effect) using multivariable mixed linear and non-linear regression for normally and non-normally distributed data to account for the cluster randomization effects. Point estimates from cluster-adjusted models will be reported with 95% confidence intervals. Additionally, subgroup analysis will stratify data based on hypertension-related complications and the number of associated medications to estimate the effect of the interventions. For all two-tailed statistical tests, *p*-value < 0.05 will be considered statistically significant. We will perform all statistical analyses using R (version 4.1) and Stata software (version 17.0).

A cost-effectiveness analysis will be performed on the average total cost incurred in both arms, and incremental cost-effectiveness ratios expressed as incremental cost per (1) 1, 5, or 10 unit (mmHg) decrease in blood pressure; (2) one hospital admission reduced; (3) 1 day of hospital stay reduced over the previous 6 months among the survivors; and (4) HRQoL using data from EQ-5D-5L and mortality. We will calculate all cost data in US dollars, using the non-subsidized cost as of the study’s commencement.

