** *Physical examination (Control and intervention group)* **												
Blood pressure measurement						x			x			x
BMI						x			x			x
Blood glucose measurement						x			x			x

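### As worded, the primary comparison is a difference in changes with no baseline adjustment stated; adjusting the month-12 contrast for baseline BP would recover some precision at almost no cost

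*Protocol article*

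**What the plan says.** Three places in the protocol article bear on this.

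- **Section 3.8** (Outcome Evaluation): the primary outcome is "evaluated by changes in the SBP and DBP of the patients from baseline to final follow-up at 12 months post-intervention".
- **Section 3.13** (Statistical Analysis): "A multilevel mixed model will be used to compare the differential changes in each outcome across the time points (T1, T3, and T5". The same paragraph describes the analysis of group changes "with individual pharmacies treated as a random effect) using multivariable mixed linear and non-linear regression". Pharmacy is the only random effect named, and no covariate is named.
- **Table 2**: T1 is month 0, T3 is month 6 and T5 is month 12. BP is scheduled at all three under "Physical examination (Control and intervention group", so every patient in both arms should have a baseline reading.

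The labels are not consistent. Section 3.6 places the two counselling sessions "once at the baseline or first visit (T0) and once at the sixth month (T1", so T1 means month 6 there and month 0 in Table 2. The set T1, T3, T5 in Section 3.13 makes sense only with the Table 2 labels, which are used below.

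Nothing in the article says whether the arms' baseline means are free or constrained to be equal, or whether baseline BP enters as a covariate.

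**The concern.** The stated target is a difference between arms in how much BP changes, with baseline as one of the modelled occasions. If each arm has its own baseline mean, the model estimates (difference at month 12) minus (difference at month 0). That contrast contains the full noise of the baseline difference. It also subtracts any chance baseline gap in full, although part of such a gap would be expected to fade by month 12.

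The number of pharmacies is limited: 40 in Bangladesh, 20 per arm. With clusters of 90, precision depends mainly on pharmacies rather than patients, so chance gaps in mean BP between arms are to be expected and further precision is hard to buy by recruitment. Baseline BP is already being collected, so adjustment needs no new data.

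**Working it through.** **1. The plan's own figure.** Inputs from Section 3.1: "According to a 4.65% BP reduction with a standard deviation of 49.78", and "the estimated sample size for Bangladesh is around 3600 at 80% power and 5% significance". Two-sided and 1:1:

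n per arm = 2 × (1.960 + 0.842)² × 49.78² / 4.65² ≈ 1799.1, rounded up to 1800, so 3600 in total.

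The figure reproduces. It contains no baseline correlation, and the article does not say whether 49.78 is the SD of a change or of a single reading. The point below concerns the analysis and leaves 3600 as it stands.

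**2. Variance of the two estimates.** Let V be the variance of a pharmacy mean at one time point, J = 20 pharmacies per arm, and r the correlation between a pharmacy's baseline and 12-month means.

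- Change score: (2V/J) × 2(1 − r)
- Baseline-adjusted: (2V/J) × (1 − r²)
- Ratio, adjusted to change: (1 − r²) / [2(1 − r)] = (1 + r)/2

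**3. Does a three-occasion mixed model behave like this?** A generalised least squares calculation was run for T1, T3 and T5 with 20 pharmacies per arm, 90 patients each and complete data. It covered ICC 0.01–0.10, patient correlation 0.4–0.8 and pharmacy stability 0.6–0.95. With baseline means free in each arm, the T1-to-T5 contrast had exactly the change-score variance (ratio 1.000). With baseline means constrained equal, the same model had exactly the baseline-adjusted variance (ratio 1.000). The loss therefore comes from the free baseline means and not from having T1 on the outcome side. Over that grid the avoidable share of the variance was about 3% to 25%.

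**4. Size.** The documents give no ICC, stability or patient correlation, so these are assumptions:

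r = [90 × ICC × stability + (1 − ICC) × patient correlation] / (1 + 89 × ICC)

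| ICC | Stability | Patient correlation | r | Ratio (1+r)/2 | Variance saved |
|---|---|---|---|---|---|
| 0.01 | 0.6 | 0.4 | 0.50 | 0.75 | 25% |
| 0.05 | 0.6 | 0.5 | 0.58 | 0.79 | 21% |
| 0.05 | 0.8 | 0.5 | 0.75 | 0.87 | 13% |
| 0.05 | 0.9 | 0.6 | 0.85 | 0.92 | 8% |

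**5. Cost of estimating the slope.** With 40 pharmacies, estimating a pharmacy-mean slope inflates the adjusted variance by about 1 + 1/(40 − 4) = 1.028. The extremes become 0.75 × 1.028 = 0.77 and 0.92 × 1.028 = 0.95, so the saving is about 5–23%.

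**6. Illustration in mmHg.** Assume SD 20 mmHg (not in the documents), ICC 0.05, stability 0.6 and patient correlation 0.5. Then V = 400 × (0.05 + 0.95/90) = 24.2.

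- Change score: SE = √(2 × 24.2 × 2 × 0.417 / 20) = 1.42 mmHg; power for 4 mmHg about 80%.
- Adjusted: SE = √(2 × 24.2 × 0.661 / 20) = 1.26 mmHg; power about 89%. With the slope cost, SE = 1.26 × √1.028 = 1.28 and power is about 88%.

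At stability 0.8, power for 3 mmHg goes from about 77% to 83% before the slope cost. These powers use a normal reference.

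**7. Carry-forward of a chance gap.** The change score subtracts the whole baseline difference; the adjusted estimate subtracts r times it. In the first illustration the baseline difference has SE √(2 × 24.2 / 20) = 1.56 mmHg. A one-SE gap is therefore over-corrected by (1 − 0.58) × 1.56 ≈ 0.65 mmHg. Over repeated randomisations this averages to zero.

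**The case against.** The strongest reply is that the text is incomplete rather than wrong. A change endpoint does not dictate a change-score analysis: regressing change on arm plus baseline gives the same treatment effect as regressing the 12-month value on arm plus baseline, so Section 3.8 alone does not exclude adjustment. The regression in Section 3.13 is described as multivariable, baseline BP could be one of the variables, and a covariate list is something an article may leave to the analysis plan. All of that stands, and it prevents any claim that adjustment has been ruled out. It does not dispose of the point, because Section 3.13 positively names differential change across T1, T3 and T5 as what the arms are compared on, and a model with free baseline means is the ordinary way to carry that out.

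Some stronger readings are tempting and should be resisted.

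- *Putting T1 among the outcomes is itself an error.* It is not; with equal baseline means that model is as efficient as adjustment.
- *The estimate is biased, or the sample size is wrong.* Under randomisation the free-means contrast is unbiased, and 3600 reproduces on its stated inputs.
- *A change score can never be the more precise choice.* Once the slope must be estimated from 40 pharmacies, the two break even where (1 + r)/2 × 1.028 = 1, that is at r of about 0.95. This lies above the range assumed here, but the absolute statement is not true.

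A further caution concerns the remedy. Section 3.4 says that treated and control pharmacies will be chosen from considerably different locations. Table 2 places consent before randomisation, which limits recruitment bias, but if location produces systematic baseline differences, a common mean at T1 would be misspecified. Covariate adjustment is the safer primary choice, although it would not fully remove such a difference either.

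**Conclusion.** The point holds as one of efficiency. On the natural reading of Section 3.13, the 12-month contrast has change-score variance, and adjustment for a baseline value already collected in both arms would lower it by roughly 5–23% after the slope cost (8–25% before). The size rests on the assumed ICC, pharmacy stability and patient correlation, and shrinks as r rises; the 80% to 89% illustration uses the lowest stability assumed and an SD of 20 mmHg that is not in the documents. If the intended model already adjusts for baseline BP, or constrains the arms to a common T1 mean, nothing is lost and only the wording needs to change. It is worth correcting because the change is nearly free and the number of pharmacies is limited, not because the planned comparison is invalid.

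**What to change.** In Section 3.13, state the primary estimate for SBP and for DBP as the between-arm difference at month 12 from the mixed model, adjusted for the patient's own baseline value and the pharmacy's mean baseline value. Month 6 can stay in the model as a further occasion. A common arm mean at T1 may be offered as an alternative only if the arms can be taken as exchangeable at baseline, given the different locations described in Section 3.4. Apply the same adjustment to the other continuous outcomes measured at month 0, and report unadjusted changes descriptively. Align the T0/T1 labels in Section 3.6 with Table 2, so that the modelled occasions are unambiguous.

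The cost is wording and a small loss of degrees of freedom. No new data, patients or pharmacies are needed.

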### 3.3. Randomization

Community pharmacies will then be randomized to one of two parallel groups (allocation ratio 1:1) using a computer-generated random number sequence. Participants and pharmacies will be assigned to intervention and control groups in a 1:1 ratio. To reach the target sample, every pharmacy needs to recruit 90 hypotensive patients. The randomization and study procedure are presented in Figure 1.

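### The primary blood pressure analysis compares changes from baseline with no stated baseline adjustment: valid, but it forgoes a modest precision gain from data already collected

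*Protocol article*

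**What the plan says.** Protocol article, section 3.8, sets the primary outcome as the change in SBP and DBP from baseline to 12 months.

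Section 3.13 plans a multilevel mixed model to "compare the differential changes in each outcome across the time points (T1, T3, and T5"). In Table 2 these visits are months 0, 6 and 12, with BP measured in both arms at each. Table 2 marks the primary outcome at month 6 as well as month 12.

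Section 3.13 continues: "We will analyze group changes (with individual pharmacies treated as a random effect"), the stated purpose being to allow for cluster randomisation. No other random effect is named. Nothing says whether baseline BP is a covariate or whether the arms share a baseline mean. Section 3.10 links each patient's records across visits, so the same people are measured repeatedly.

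On the design, section 3.3 says "Community pharmacies will then be randomized to one of two parallel groups (allocation ratio 1:1"). Section 3.1 gives 20 pharmacies in each of two Bangladeshi subdistricts and an average of 90 patients per pharmacy.

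**The concern.** Baseline BP is collected on every patient, and there are two ways to use it. Subtracting it fixes the weight on baseline at 1. Adjusting for it lets the data choose the weight. When the correlation between baseline and follow-up is below 1, subtraction carries some baseline noise into the treatment contrast and adjustment removes it. The gain needs no further patients or measurements.

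There is also a conditional issue. A longitudinal model for BP levels with three visits per patient needs terms for two things: the correlation of a patient's own values, and movement of pharmacy means over time. Without the first, the standard error of a change contrast is too large. Without the second, it is too small. What is at stake is the width and the coverage of the primary confidence interval.

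**Working it through.** **The plan's own figure.** Inputs from section 3.1: difference 4.65, SD 49.78 ("According to a 4.65% BP reduction with a standard deviation of 49.78"), 80% power, 5% significance. Section 3.13 makes tests two-tailed. Per arm, n = 2(1.960 + 0.842)² × 49.78² / 4.65² = 2 × 7.849 × 2478.05 / 21.62 ≈ 1,799, rounded up to 1,800. The total is 3,600 = 40 pharmacies × 90, as stated. The formula contains no term for baseline correlation, so the calculation takes no credit for baseline BP.

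**Assumptions.** The article gives no correlations. I use an ICC of 0.01 or 0.05, a correlation of pharmacy effects over time (CAC) of 1.0 or 0.8, and a within-patient correlation ρ of 0.3 to 0.7. With total variance 1 and m = 90:

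- stable pharmacy effect c = ICC × CAC
- pharmacy-by-time effect d = ICC × (1 − CAC)
- patient effect p = ρ(1 − ICC)
- residual e = (1 − ρ)(1 − ICC)

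**Step 1: adjustment against change, at pharmacy-mean level.** The variance of a pharmacy mean is V = c + d + (p + e)/m. The covariance between visits is C = c + p/m, so r = C/V. Adjusted variance over change-score variance is (1 − r²)/[2(1 − r)] = (1 + r)/2.

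- ICC 0.01, CAC 0.8, ρ 0.3: V = 0.0210, C = 0.0113, r = 0.54, ratio 0.77.
- ICC 0.05, CAC 0.8, ρ 0.5: V = 0.0606, C = 0.0453, r = 0.75, ratio 0.87.
- ICC 0.05, CAC 1.0, ρ 0.7: V = 0.0606, C = 0.0574, r = 0.95, ratio 0.97.

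The first and last are the extremes of the assumed grid, so the saving is about 3% to 23% of variance. Since √0.77 = 0.88 and √0.97 = 0.98, the interval is about 2% to 12% narrower. At patient level with ρ = 0.5 the ratio is (1 + 0.5)/2 = 0.75, a 25% saving.

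**Step 2: how baseline must enter.** Step 1 assumes that the slope on pharmacy means is free. If only the patient's own baseline is entered, one slope b serves both levels. With 90 patients per pharmacy it will lie near ρ. The variance is then V(1 + b²) − 2bC, against 2(V − C) for change.

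- ICC 0.01, CAC 0.8, ρ 0.3: (0.02289 − 0.00678)/0.0194 = 0.83, still a gain.
- ICC 0.05, CAC 1.0, ρ 0.5, C = 0.05528: (0.07569 − 0.05528)/0.01056 = 1.93, a loss.

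So the pharmacy mean of baseline BP has to be in the model too.

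**Step 3: standard errors under two readings.**

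*One change score per patient, pharmacy intercept.* The stable pharmacy and patient effects cancel. The pharmacy intercept on change has variance 2d, and a pharmacy-mean change has variance 2d + 2e/m, which equals 2(V − C). The standard error is valid.

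*Three BP levels per patient, pharmacy intercept only.* For month 12 minus baseline, true variance over model variance is (md + e)/(p + e + d). With a patient intercept added it is (md + e)/(e + d). Type I error is 2[1 − Φ(1.96/√ratio)]. At ρ = 0.5, with ICC 0.03 and CAC 0.6 added to the grid:

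| ICC | CAC | Pharmacy only: ratio | Type I | With patient intercept: type I |
|---|---|---|---|---|
| any | 1.0 | 0.50 | 0.6% | 5.0% |
| 0.01 | 0.8 | 0.68 | 1.8% | 9.3% |
| 0.03 | 0.8 | 1.05 | 5.6% | 17.5% |
| 0.05 | 0.8 | 1.43 | 10% | 24% |
| 0.03 | 0.6 | 1.59 | 12% | 27% |

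The pharmacy-only model turns from conservative to anti-conservative at (m − 1)d = p. At ICC 0.03 that is d = 0.485/89 = 0.0054, a CAC of about 0.82.

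**The case against.** A reader might infer that the stated model gives wrong standard errors. The documents do not support that. The wording about group changes, read with the outcome definition in section 3.8, fits one change score per patient with a pharmacy intercept, which step 3 shows to be valid. Even on the three-visit reading, a multilevel model leaves room for a patient level. The remark about pharmacies explains how clustering is handled and does not claim to list every random effect. A condensed article may leave the covariance structure to the analysis plan. The direction is not fixed either: with ICC 0.03 and CAC 0.8, the pharmacy-only model is almost nominal at 5.6%. This objection stands, so the standard-error point is conditional only.

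A reader might also take 25% as the expected gain. That is a patient-level figure; with pharmacies randomised, the pharmacy-mean range of 3% to 23% is the relevant one. The loss would also vanish if the three-visit model already held the arms to a common baseline mean with suitable random effects. The article neither says nor excludes this.

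Finally, the lack of a country or subdistrict term might look like a defect. Section 3.3 describes no stratified randomisation, omitting area does not bias the contrast, and a covariate list can be left to the analysis plan.

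What survives is that the article frames its primary comparison as one of changes and states no baseline adjustment.

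**Conclusion.** The point holds as an efficiency improvement. The planned comparison of changes is valid. Adjusting for baseline BP would reduce the variance of the primary contrast by about 3% to 23%. In terms of the 40 Bangladeshi pharmacies, about 31 (40 × 0.77) to 39 (40 × 0.97) analysed with adjustment would match 40 analysed by change. The gain is largest when the ICC is small and the within-patient correlation low. It is close to nil when pharmacy effects are large and stable.

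The risk of a misstated standard error applies only if BP levels at three visits are fitted with too few random effects. Then a pharmacy intercept alone is conservative when pharmacy effects are stable and anti-conservative when they drift enough. A patient intercept added alone is correct if they are stable and anti-conservative if they drift. All these sizes rest on assumed ICCs and correlations.

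**What to change.** State the primary analysis as 12-month BP (SBP and DBP separately) in a linear mixed model with arm and baseline BP as fixed effects, pharmacy as a random intercept, and Kenward-Roger or Satterthwaite degrees of freedom. Enter baseline BP as both the pharmacy mean and the patient's deviation from it, for the reason in step 2.

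If the three-visit model is kept, constrain the arms to a common baseline mean, include patient and pharmacy-by-time random effects, and name the month-12 arm contrast as primary.

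The cost is one model statement, with no extra patients or data. The first option spends one of the 38 between-pharmacy degrees of freedom (40 − 2) in Bangladesh on the pharmacy-mean slope. The second is a slightly more complex model.

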### 3.5. Training of the Pharmacists

Mandatory communication training will enhance treatment integrity since pharmacist skills and competences will determine the quality of the intervention. Before the study begins, CPs in the intervention arm will receive training involving both theoretical and practical sessions. It will cover the prevalence, risk factors, complications, and diagnosis of hypertension, as well as non-pharmacological ways of preventing it. On the practical side, CPs will learn how to measure blood pressure using a manual sphygmomanometer, interpret the measurements, and educate and counsel hypertensive patients through audio–visual presentations. As part of the intervention strategy, blood pressure control, the identification of hypertension-related complications, health education, medication and lifestyle modification counseling, follow-up, and referral to a medical practitioner or hospital will be provided.

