### 3.10. Data Management

All data will be confidentially stored in computers and entered manually in spreadsheets. Findings will be available to authorized individuals for analysis and reporting purposes only. To ensure the privacy and accuracy of the study data, the datasheets will be in a password-protected server, and data entry will be reconfirmed and double-checked for any potential errors during input. The research data will be published in a manner that ensures participants’ anonymity. A unique identifier will be used to coordinate participants’ data across baseline and all follow-up stages. Patients will be coded as numbers, with the code key stored in a password-protected document, ensuring all safety precautions. The patients who will complete all the scheduled follow-ups will be included in the analysis of results. To avoid a withdrawal bias, a strict intention-to-treat technique will be considered in our analysis. Furthermore, the variable imputation method will be used to handle the missing data. After each intervention, an interim analysis will be performed by the main investigator.

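### The primary model names only a time-constant pharmacy effect; if repeated BP values are the response, it drops out of the change contrast and pharmacy-level variation in change goes unmodelled

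*Protocol article*

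**What the plan says.** Section 3.1 fixes the unit of allocation: "Randomization clusters are community pharmacies". Section 3.8 defines the primary outcome as "changes in the SBP and DBP of the patients from baseline to final follow-up at 12 months post-intervention". Section 3.10 makes clear that the same patients are followed: "A unique identifier will be used to coordinate participants’ data across baseline and all follow-up stages".

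Section 3.13 then gives the analysis in two sentences. The first states the comparison: "A multilevel mixed model will be used to compare the differential changes in each outcome across the time points (T1, T3, and T5". The second names the clustering term, "We will analyze group changes (with individual pharmacies treated as a random effect) using multivariable mixed linear and non-linear regression", and gives its purpose: "to account for the cluster randomization effects". Pharmacy is the only random effect named. No patient-level or pharmacy-by-time effect is named, and none is ruled out.

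In Table 2, T1 is month 0, T3 is month 6 and T5 is month 12, and BP is measured at all three. (Section 3.6 uses T0 and T1 for baseline and month 6, but the sequence in Section 3.13 exists only in Table 2.)

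**The concern.** A pharmacy intercept shifts all readings from a pharmacy by the same amount at every visit. It is the right device for comparing levels between arms. For a change between two visits it subtracts out. What matters for a change contrast in a cluster-randomized trial is how far pharmacies differ in their change, and a single intercept has no place for that.

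If the model is fitted to repeated BP values as named, two things go unmodelled. Leaving out pharmacy-by-time variation makes the standard error too small. Leaving out the correlation among a patient's own readings makes it too large. The net error depends on unknown variance components, so the 95% intervals and p-values for SBP and DBP would be right only by coincidence. Section 3.13 applies the same model to the secondary outcomes.

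**Working it through.** **Inputs from the protocol.** Section 3.1 gives 20 pharmacies in each of two subdistricts, so 40 in Bangladesh. With 1:1 allocation (Section 3.3), k = 20 per arm. The average number of patients per pharmacy is m = 90. As a check, an effect of 4.65 with SD 49.78, 80% power and two-sided 5% gives n per arm = 2 × (1.960 + 0.842)² × 49.78² / 4.65² ≈ 1,800, so 3,600 in total. This reproduces the stated figure and equals 20 × 90 per arm. The present point does not alter that figure.

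**Assumed inputs (not in the protocol).** ICC 0.01-0.05; cluster autocorrelation (CAC, the share of pharmacy variance that is stable over time) 0.5-1.0; within-patient correlation r 0.3-0.7. Total variance is set to 1.

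**Variance components.**
- Pharmacy, stable: ICC × CAC
- Pharmacy-by-time, σ²ct: ICC × (1 − CAC)
- Patient, σ²p: (1 − ICC) × r
- Residual, σ²e: (1 − ICC) × (1 − r)

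**What cancels.** Write a reading as fixed effects + c (pharmacy) + ct (pharmacy-by-time) + p (patient) + e. In T5 minus T1, both c and p disappear. The differences in ct and e remain.

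**Variance of the arm difference in change.**
- True: (2/k) × [2σ²ct + 2σ²e/m]
- Reported by the pharmacy-intercept model (approximate): (2/k) × [2(σ²p + σ²e + σ²ct)/m]
- Reported with a patient intercept added (approximate): (2/k) × [2(σ²e + σ²ct)/m]
- Actual type I error = 2 × [1 − Φ(1.96 × reported SE / true SE)]

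**Worked case: ICC 0.05, CAC 0.8, r 0.5.** Here σ²ct = 0.01, σ²p = 0.475 and σ²e = 0.475.
- True variance: 0.1 × (0.02 + 0.95/90) = 0.003056, SE 0.0553
- Pharmacy only: 0.1 × (1.92/90) = 0.002133, SE 0.0462; ratio 0.836; type I error 10.1%
- Patient intercept added: 0.1 × (0.97/90) = 0.001078, SE 0.0328; ratio 0.594; type I error 24.4%

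With an assumed SD of 20 mmHg the three SEs are 1.11, 0.92 and 0.66 mmHg.

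**Other settings, closed form.**

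| ICC | CAC | r | Pharmacy only | Patient intercept added |
|---|---|---|---|---|
| 0.01 | 1.0 | 0.7 | 0.03% | 5.0% |
| 0.05 | 1.0 | 0.5 | 0.6% | 5.0% |
| 0.01 | 0.8 | 0.5 | 1.8% | 9.3% |
| 0.02 | 0.8 | 0.5 | 3.5% | 13.5% |
| 0.05 | 0.9 | 0.5 | 4.6% | 15.8% |
| 0.05 | 0.5 | 0.5 | 24.1% | 40.1% |
| 0.05 | 0.5 | 0.3 | 25.7% | 34.0% |
| 0.05 | 0.5 | 0.7 | 22.4% | 49.3% |

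Over the whole grid the ratio of reported to true SE for the pharmacy-only model runs from 0.58 to 1.83.

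**Checks.** With 20,000 simulated trials per setting, using the closed-form reported SE, rejection was 10.0% in the worked case, 24.3% at ICC 0.05 and CAC 0.5, and 0.5% at ICC 0.05 and CAC 1.0 (all r 0.5). Mixed models fitted to 60 simulated trials in each of four settings had mean reported SEs within 0.0003 of the closed form (0.0459 against 0.0462 in the worked case). Sixty trials are too few to estimate rejection rates well. In the 20,000-trial runs, a t-test on pharmacy-level mean changes with 38 degrees of freedom rejected in 4.8% to 5.4% of trials in every setting tried.

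**The case against.** The strongest reply is that the text also fits a valid model. It speaks of analysing group changes with pharmacy as a random effect, the primary outcome is itself a change, and Table 2 marks that change at months 6 and 12 only. If the response is one 12-month change per patient, the pharmacy effect is a pharmacy-level effect on change, does not cancel, and is the right clustering term. Baseline might be listed only because it is needed to compute the change. This stands as a possible reading. Against it, a change score does not exist at T1, so naming T1 among the compared time points points to repeated values. The text does not decide between them.

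Second, the protocol never says that pharmacy is the sole random effect, and an article may leave the full covariance structure to an analysis plan. That is fair, and silence on REML or degrees of freedom is no fault. But the term that is named carries a stated purpose, and under the more natural reading it does not serve that purpose. Taking the word multilevel to imply a patient intercept does not help unless CAC is 1.

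Third, a reader might infer that the intervals will be far too narrow and a false claim of benefit likely. The documents do not support that. With the pharmacy effect alone the test is conservative in several plausible settings and nearly nominal in others. The Section 3.5 remark that "pharmacist skills and competences will determine the quality of the intervention" does not settle it either. It explains why intervention pharmacists are trained, and says nothing about drift in control pharmacies or in the absence of an effect, which is what the type I error figures assume.

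**Conclusion.** The point holds conditionally. If Section 3.13 means repeated BP values with the named pharmacy intercept, pharmacy variation in change is not accounted for and the standard error is generally miscalibrated, in a direction that cannot be known from the protocol. Under the assumed ranges, actual type I error against a nominal 5% runs from 0.03% to 25.7% for the pharmacy-only model. With a patient intercept added it is 5% at CAC 1 and rises to 49.3% at the far end. If the response is each patient's change, the pharmacy effect is adequate.

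It would go too far to say that the pharmacy effect cancels from any analysis of change, or that the reported intervals are certainly wrong. What the text supports is that one reading of the primary analysis is sound, the reading its wording favours is not, and the choice is left open. All error rates rest on assumed ICC, CAC and within-patient correlation and apply to the 40 Bangladesh pharmacies. This deserves correction before analysis, but it is an important clarification rather than a demonstrated fatal error.

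**What to change.** State the primary analysis as 12-month SBP (and likewise DBP) regressed on arm and the patient's baseline value, with a pharmacy random intercept. With one outcome reading per patient that intercept is the correct clustering term, and the baseline value is already collected. An analysis of each patient's 12-month change with a pharmacy random effect would also be valid if the authors prefer to keep change as the response; it should then be stated as such.

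If all visits are to be modelled jointly, include a patient random effect (or an unstructured within-patient covariance) and a pharmacy-by-time random effect.

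In each case use small-sample degrees of freedom based on the number of pharmacies, about 38 for Bangladesh (40 pharmacies minus 2 arms). Carry the same structure to the secondary outcomes.

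The cost is a few lines of wording and code, with no change to data collection. The downside is that the reported interval may be wider than the one the stated model would print.
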